**Psychological impact**				
*Feelings about genomic testing results*	Feelings About Genomic Testing Results (FACToR) [44]	**–**	**X**	**X**
*Uncertainty*	Perceptions of Uncertainties in Genomic Sequencing (PUGS) [45]; FACToR subscale [44]	**–**	**X**	**X**
*Depression*	8-item Patient Health Questionnaire depression scale (PHQ-8) [46]	**X**	**X**	**X**
*Anxiety*	Generalized Anxiety Disorder Screener (GAD-2) [47, 48]	**X**	**X**	**X**
*Perceived stress*	Perceived Stress Scale 4-item (PSS-4) [49]	**X**	**X**	**X**
*Self-efficacy*	Decision Self-Efficacy Scale [50]	**X**	**–**	**–**
*Patient activation*	Short Form Patient Activation Measure (PAM) [51]	**X**	**–**	**–**
*Decisional regret*	Decision Regret Scale [52]	**–**	**X**	**X**
**Behavioral impact**				
*Information seeking*	CSER developed measure (novel); Adapted from Psychological Adaptation to Genetic Information Scale [53]	**–**	**X**	**X**
*Family communication*	CSER developed measure (novel)	**–**	**–**	**X**
**Social impact**				
*Support*	Low-Literacy Decisional Conflict Scale (Q6 and Q8) [54]	**X**	**X**	**X**
*Access to care*	CSER developed measure (novel)	**X**	**X**	**X**
*Life chaos*	Chaos Scale [55]	**X**	**–**	**–**
*Family and community*	Medical Outcomes Study Social Support Survey (mMOS-SS) [56]	**X**	**–**	**–**
*Quality of life ascertainment (for child)*	PedsQL Parent Proxy Generic Core [57]; EuroQol-Visual Analog Scale (VAS) [58]	**X**	**–**	**X**
**Economic impact**				
*Cost/value*	CSER developed measure (novel)	**–**	**X**	**X**
*Healthcare utilization*	Self-reported Utilization of Health Care Services [59]	**–**	**X**	**X**
**Sociodemographic factors**				
*Literacy; numeracy*	BRIEF Health Literacy Survey [60]; Subjective Numeracy Scale (SNS-3) [61]	**X**	**–**	**–**
*History of receiving genetic testing*	Adapted from the GUARDD study [37]	**X**	**–**	**–**
*Trust in healthcare system*	CSER developed measure (novel) adapted from Health Care System Distrust Scale [62]	**X**	**–**	**–**
*Health beliefs*	Brief Illness Perception Questionnaire (IPQ) [63]	**X**	**–**	**–**
*Child and parent: sex, age, race/ethnicity, country of origin, language, insurance status, residential history, zip code*	CSER developed measure (novel); Adapted from HCHS/SOL Personal Information Questionnaire [64]	**X**	**–**	**–**
*Parent only: education level, employment, income, household, marital status*	CSER developed measure (novel); Adapted from HCHS/SOL Personal Information Questionnaire [64]	**X**	**–**	**–**
*Grandparents of child: residential history*	Adapted from HCHS/SOL Personal Information Questionnaire [64]	**X**	**–**	

^1^BL = baseline survey

^2^ROR1 = return of results, visit 1 survey

^3^ROR2 = return of results, visit 2 survey

#### Pilot study measures

The quantitative outcome sought from the GenomeDiver intervention is whether it led to an increase in the rate at which the genetic test yields a clinical diagnosis compared with SOC. We are also testing other outcomes. Laboratory personnel will be asked to assess how long analyses took for individual patients; how many variants were considered per patient; whether they gained insights into the ability of clinical colleagues to identify specific phenotypes; and whether the prospective GenomeDiver intervention overall changed the time to issue a report, as a concern is that introducing a delay in analyzing the VCF file while waiting for GenomeDiver input could lead to the report being overdue. Clinicians will be asked whether the HPO terms appeared to be appropriate for the presentation using yes, no, or maybe designations; the time spent performing sessions; the diagnostic value and ease of interpretation of HPO terms; whether any further testing was prompted by the suggested HPO terms; and any difficulty categorizing specific HPO terms because of the race/ethnicity of the patient. The analysis will also include testing whether the referring provider’s specialty or patient properties, such as age, number of notes in the electronic medical record, or length of time in the health care system are associated with the HPO term categorization patterns.

#### Diagnostic yield and comparison of WGS to TGP

The overall diagnostic yield of the genomic testing will be calculated as the percentage of NYCKidSeq participants with definitive or likely positive diagnoses. Individual diagnostic yield will be calculated for WGS and TGP tests as well as by disease category (neurology, cardiology, immunology). We will also investigate the concordance between the two testing modalities. Lastly, we will assess the diagnostic yield of both tests among race/ethnic groups. Genomic testing result categorization for both testing modalities is maintained in the REDCap database.

### Confidentiality

Genetic counselors and other study clinicians access the participants’ medical record to obtain relevant clinical information, such as medical diagnoses and previous genetic test results. This information is reviewed and collected in accordance with the Health Insurance Portability and Accountability Act (HIPAA). The following procedures are used at MS and EM to safeguard data: (1) train staff on data sensitivity and safeguards; (2) store and process sensitive hard copy in a centralized location; (3) secure sensitive hard copy in locked files when not in use; (4) remove names, addresses, and other direct identifiers from hard copy and computer-readable data if they are not necessary for participant tracking; (5) destroy all identifiable links to data after accuracy has been verified and final analyses have been completed; and (6) protect the patient information file, secured in our file server, by Microsoft NT-encrypted password and a separate password to access the database file on the server.

Limited identifying information of consented participants is stored in a web-based REDCap database. The REDCap server is managed by Mount Sinai IT and is firewall protected. User access to the database for study personnel is managed by the study project manager. Data access for study personnel is limited to their site's participants and what is required for their roles on the project. The NYCKidSeq program gives participants the option to consent to share de-identified genetic and related clinical information with other CSER investigators and access-restricted scientific databases.

As this study involves genetic testing for diagnostic purposes, WGS and TGP results are entered into the medical record along with the accompanying genetic counseling chart notes. These documents are maintained in the participant’s permanent medical record. The remaining clinical research records including IRB documentation are retained for at least 3 years at MS and at least 25 years at EM after the clinical research study is completed, consistent with NIH and FDA policies, or longer if required by MS. Upon completion of this period, documents will be shredded and disposed of in accordance with hospital requirements.

### Analysis of outcomes

#### Lead-in phase

Data from the feedback sessions of parents performed during the lead-in phase of the study (*N* = 30) to learn about GUÍA (*N* = 15) and to identify any issues with the surveys (*N* = 15) will be reviewed. Any useful feedback from these sessions will be incorporated into GUÍA and the surveys.

#### RCT

Descriptive statistics will be calculated for quantitative survey instruments in the baseline, ROR1, and ROR2 surveys. In the case of missing data, when survey measures contain summary scores, a mean score will be calculated based on the responses provided. We will adjust for covariates, including age, sex, and race/ethnicity where appropriate. Repeated measures of analysis of variance (ANOVAs), chi-squared test, or regression models will be fit to the data in a simple paired design (*N* = 550 on each arm) to assess and identify significant improvements in parental understanding, satisfaction, and feelings about the results, and their subsequent behavior in the SOC group compared to the GUÍA group. A statistical significance criterion of *p* < 0.05 (after adjustment for multiple testing) will be used for all analyses.

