### Study outcomes

#### RCT survey measures

The NYCKidSeq project is assessing participant outcomes through surveys administered at BL, prior to pre-test counseling and consent for the genomic testing, following the result disclosure genetic counseling during ROR1, and 6 months after disclosure of results at ROR2. The primary study outcome is the participant’s perceived understanding of genomic testing results, with comparison of results in SOC arm to GUÍA arm. The secondary study outcomes are objective understanding of genomic testing results and understanding of medical follow-up, the actionability of genomic results, and adherence to medical follow-up recommendations, with comparison of results in SOC arm to GUÍA arm. Additional participant outcomes focus on six domains: (a) attitudes toward genomic testing, (b) perceived utility, (c) psychological, (d) behavioral, (e) social, and (f) economic impact of genomic testing. With the exception of economic impact, all outcomes will be compared between the two study arms. The CSER consortium harmonized survey measures so that CSER projects, when possible, administer standardized survey measures [25] to facilitate combining data into a single data set for cross-consortium analysis. Table 2 summarizes participant outcomes being assessed across the three time points. When possible, previously validated measures were used. The BL and ROR1 surveys are administered in-person by a study staff member while the ROR2 survey is administered by a study staff member over the phone or video. Surveys are administered in either English or Spanish. All survey response data is entered and maintained in the REDCap database.

**Table 2 Tab2:** NYCKidSeq participant outcomes by survey timepoint

Variable	Source	BL^**1**^	ROR1^**2**^	ROR2^**3**^

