**Secondary outcomes**				
*Objective understanding of genomic testing results*	NYCKidSeq developed measure (novel)	**–**	**X**	**X**
*Medical actions and non-medical/patient-initiated actions attributable to genomic testing*	CSER developed measures (novel): Attributable to Genomic Testing (RMA) and Patient-Initiated Actions Attributable to Genomic Testing (PIA)	**–**	**–**	**X**

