## Discussion

The NYCKidSeq study aims to recruit 1130 children and their families, predominantly from Harlem and the Bronx areas of NYC to a RCT. Recruitment began on January 31, 2019, and is expected to be completed by May 31, 2021. Eligible children are suspected of having an undiagnosed genetic disorder in three disease categories: neurologic, cardiovascular, and immunologic. Two clinical genetic tests will be performed for each participant, either proband, duo or trio WGS (depending on sample availability) and proband TGPs. Clinical utility, cost, and diagnostic yield of both testing modalities will be assessed and compared. This study will evaluate the use of a novel, digital platform called GUÍA to digitize and standardize the return of genomic results and improve participant understanding, designed for both English- and Spanish-speaking families. The outcomes are parental understanding of and attitudes toward receiving genomic test results for their child, and behavioral, psychological, and social impact of genomic results. We will also conduct a pilot study to assess a digital tool called GenomeDiver designed to enhance communication between medical professionals and genetic testing labs, and evaluate its ability to increase diagnostic yield when used as a means to improve communication to share phenotypic and genotypic information, compared to standard practices.

There are several limitations to the study design, which includes the lack of blinding in the RCT. Participants and study staff are aware of participants’ randomization status as participants in the intervention arm are asked about their experiences using GUÍA specifically. In addition, GUÍA is unavailable in languages other than English and Spanish. After evaluating the use of GUÍA in these languages, we hope to expand the usability of GUÍA in other languages to be more reflective of the immense linguistic diversity of NYC.

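### Averaging only the answered items suits a knowledge score badly: objective understanding should be exempt, with unanswered items scored as not correct

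*Protocol article*

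**What the plan says.** The protocol article, under Analysis of outcomes, RCT, gives a single instruction for incomplete questionnaires: "In the case of missing data, when survey measures contain summary scores, a mean score will be calculated based on the responses provided". It covers all survey measures that have a summary score and names no exception.

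One of the outcomes with no exception is a knowledge measure. Under RCT survey measures the article states: "The secondary study outcomes are objective understanding of genomic testing results and understanding of medical follow-up", to be compared between the SOC and GUÍA arms. Table 2 lists "Objective understanding of genomic testing results" as a new instrument developed by the study, given at the result-disclosure visit (ROR1) and the six-month follow-up (ROR2). The number of items, the marking, and the handling of a don't-know answer are not described.

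Three other statements bear on the point:
- The primary outcome is a different, self-rated measure: "The primary study outcome is the participant’s perceived understanding of genomic testing results".
- Surveys are given by staff: "The BL and ROR1 surveys are administered in-person by a study staff member while the ROR2 survey is administered by a study staff member", by phone or video.
- The trial is open: "Participants and study staff are aware of participants’ randomization status".

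**The concern.** Averaging the answered items assumes that a person's unanswered items would have looked like the answered ones. For an attitude or mood scale that is often acceptable. For a test of knowledge it fails when an item is left blank because the parent does not know the answer. The item leaves the denominator, and the parent scores higher than if it had been marked.

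The comparison between arms is exposed because GUÍA is meant to improve understanding, so the number of unknown items, and with it the number of blanks tied to not knowing, is expected to differ by arm. The tendency to leave an unknown item blank could also differ by arm in an open trial. At stake is the size, and possibly the direction, of the effect on the first-named secondary outcome. That outcome is the natural companion to a self-rated primary outcome, although the article does not give it that role in so many words.

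**Working it through.** **The plan's own figures.** The article gives no item-missingness rate, effect size, standard deviation or power, so there is no figure of that kind to reproduce. The sample size is consistent: 1130 − 30 lead-in participants = 1100, and 1100 / 2 = 550 per arm.

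**Assumptions (none is in the document).** Items are marked right or wrong. Only unknown items are skipped. A parent knows a share p of the items and skips a share s of the unknown ones.

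**Formula.** The answered items are the known share p plus the unknown items attempted, (1 − p)(1 − s). Under the averaging rule the expected score is about

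score = p / [p + (1 − p)(1 − s)].

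**Effect on the level.** For p = 0.60:
- s = 0.10: 0.60 / (0.60 + 0.40 × 0.90) = 0.60 / 0.96 = 0.625
- s = 0.20: 0.60 / (0.60 + 0.40 × 0.80) = 0.60 / 0.92 = 0.652
- s = 0.50: 0.60 / (0.60 + 0.40 × 0.50) = 0.60 / 0.80 = 0.750

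**Effect on the arm difference.** The true scores are taken as 0.60 (SOC) and 0.65 (GUÍA). The last two columns come from a simulation of 1500 trials with 550 per arm, 10 items, ability varying between parents with SD 0.15, and an unadjusted two-sided 0.05 test. It differs a little from the formula because ability varies between parents.

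| Skipping, SOC / GUÍA | SOC score | GUÍA score | Difference, formula | Difference, simulated | Power |
|---|---|---|---|---|---|
| 0 / 0 | 0.600 | 0.650 | 0.050 | 0.050 | 0.98 |
| 20% / 20% | 0.652 | 0.699 | 0.047 | 0.047 | 0.97 |
| 50% / 50% | 0.750 | 0.788 | 0.038 | 0.039 | 0.92 |
| 20% / 10% | 0.652 | 0.674 | 0.021 | 0.024 | 0.47 |
| 30% / 14.6% | 0.682 | 0.685 | 0.003 | 0.007 | 0.085 |
| 10% / 30% | 0.625 | 0.726 | 0.101 | 0.097 | 1.00 |

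In the 20% / 10% row the blanks are 0.20 × 0.40 = 8% of all SOC items and 0.10 × 0.35 = 3.5% of all GUÍA items.

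**A larger true difference.** For 0.60 against 0.70 with equal 20% skipping: 0.70 / (0.70 + 0.30 × 0.80) = 0.745, and 0.745 − 0.652 = 0.093, so 9.3 of 10 points remain. With 40% skipping under SOC and 10% under GUÍA: 0.70 / 0.97 = 0.722 against 0.60 / 0.84 = 0.714, a difference of 0.7 points.

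**Attenuation is not universal.** At low true scores equal skipping can widen the gap: 0.20 against 0.25 at s = 0.50 gives 0.333 against 0.400, or 6.7 points from a true 5.

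**Blanks scored as not correct.** The expected score is then p whatever s is. In the simulation the difference stays at about 0.050 with power 0.97 to 0.98 in every row. This follows by construction, because the model lets only unknown items be skipped.

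**A minimum number of answered items.** At 30% / 14.6% skipping the simulated difference is 0.007 with no minimum, 0.006 with a 50% minimum and −0.007 with an 80% minimum. A completeness threshold does not remove this bias.

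**The case against.** The strongest reply is that the mechanism depends on facts the article does not give. The items may not be marked right or wrong. A don't-know answer may be a recorded response, in which case it stays in the denominator. Every survey is administered by staff, and the lead-in phase gathered think-aloud comments on the clarity, flow and order of the questions, so true blanks may be few. Averaging answered items is also a common way to score the multi-item scales that make up most of Table 2. All of this stands. It limits the size of the problem, but it does not make the stated rule suitable for a knowledge score.

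Some stronger readings do not stand:
- A reader might infer that the rule will erase a true benefit of GUÍA. That needs clearly more skipping under SOC, or near-total skipping of unknown items. The document supports neither the rates nor the direction, and the bias can equally exaggerate the benefit.
- A reader might take the lack of a stated minimum number of answered items as the defect. An article commonly leaves such a threshold to the full protocol or analysis plan, which are not shown, and a threshold would not cure the bias.
- A reader might object that a mean puts sum-scored scales, such as the 8-item depression scale, on the wrong metric. Applied to everyone, it is a rescaling that leaves the arm comparison unchanged, and nothing says that means and sums will be mixed.
- A reader might extend the bias to the primary outcome. That is self-rated perceived understanding, and no bias is shown for it.

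**Conclusion.** The point holds in limited form. The article states one averaging rule for all summary scores, and that rule does not suit objective understanding. If items are marked right or wrong and blanks tend to reflect not knowing, scores are inflated by about 5 points at a true 60% with 20% skipping. Equal skipping leaves most of the arm difference in place: about 4.7 of 5 points, with power 0.97. Unequal skipping can bias it either way, to about 2.4 points (power 0.47) at 20% SOC and 10% GUÍA, or about 9.7 points at 10% and 30%.

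Every score level, item count and skip rate here is assumed. If item non-response is rare, the effect is correspondingly small. The outcome concerned is secondary. The change is worth making because it is cheap and can be settled before the data are analysed.

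**What to change.** Exempt objective understanding from the averaging rule, for example with this text: *Objective-understanding items that are left blank or answered don't know are scored as not correct. A sensitivity analysis uses the mean of the answered items. Item non-response on this measure is reported by arm and visit. Other scales keep the mean of answered items, or follow the instrument's own scoring rule where it has one.*

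The cost is this short passage in the plan, a change to the scoring code and one extra analysis; no new data are needed. The drawback is that a blank caused by interruption or refusal is counted as not correct, which lowers that parent's score. The sensitivity analysis and the non-response table by arm show whether this matters.

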#### Randomized controlled trial

Participants in the RCT (*N* = 1100) are randomized using a stratified randomization scheme by disease category (cardiac, neurologic, immunologic) and clinical site as seen in Fig. 2. Randomization occurs prior to the baseline visit (BL) via a randomization module in REDCap applied by a study staff member. The REDCap randomization allocation is not revealed to study staff at any point in the study.

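### The covariate sentence names neither randomisation stratum, so standard errors may be somewhat too large; four baseline-only measures are also listed as outcomes to compare between arms

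*Protocol article*

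**What the plan says.** Under Procedures, Randomized controlled trial, the 1100 RCT participants are "randomized using a stratified randomization scheme by disease category (cardiac, neurologic, immunologic) and clinical site". With three disease categories and two recruiting institutions (MS and EM), that makes about six strata.

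Under Analysis of outcomes, RCT, the only sentence on covariates is "We will adjust for covariates, including age, sex, and race/ethnicity where appropriate". The same paragraph leaves the model open: "Repeated measures of analysis of variance (ANOVAs), chi-squared test, or regression models will be fit to the data". It sets the criterion at p < 0.05, "after adjustment for multiple testing) will be used for all analyses".

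Under Study outcomes, RCT survey measures, the rule for comparison is: "With the exception of economic impact, all outcomes will be compared between the two study arms". Table 2, which lists participant outcomes by survey visit, places four measures under outcome domains with a mark at baseline only: decision self-efficacy and patient activation (psychological impact), and life chaos and the mMOS-SS family and community support measure (social impact).

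**The concern.** Stratified randomisation balances the arms on disease category and site, which removes the between-stratum part of the variance from the difference between arms. A standard error computed as if randomisation had been unstratified still includes that part. The interval is then wider, and the test less powerful, than the design has earned. The covariates that the article does name are not the ones used to randomise. One of the permitted methods, the ordinary chi-squared test, adjusts for nothing. The qualifier *where appropriate* leaves even the named adjustments to later judgement, in a trial whose Discussion says that participants and staff know the allocation.

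The second issue is one of consistency. A measure taken once, before the intervention is delivered, cannot show an effect of it. Testing it between arms tells the reader nothing about GUÍA and adds tests to the multiplicity adjustment.

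**Working it through.** **Inputs.** From the article: 550 per arm, 2 × 550 = 1100 in the RCT, and 1100 + 30 lead-in participants = 1130, which agrees with the stated target. The article shows no effect size, SD or power, so 1100 cannot be reproduced as a power calculation. Assumed: outcome SD of 1, two-sided alpha of 0.05, and R², the share of outcome variance explained by disease category and site, shown as a range.

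**Formulas.**
- Reported SE without strata: √(2/550) = 0.0603 SD.
- SE with strata: √((1 − R²) × 2/550).
- SE excess: 1/√(1 − R²) − 1.
- True size of the unadjusted test: 2 × P(Z > 1.96/√(1 − R²)).

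| R² (assumed) | Adjusted SE | SE excess if strata ignored | True size of nominal 5% test |
|---|---|---|---|
| 0 | 0.0603 | 0% | 5.0% |
| 0.02 | 0.0597 | 1.0% | 4.8% |
| 0.05 | 0.0588 | 2.6% | 4.4% |
| 0.10 | 0.0572 | 5.4% | 3.9% |
| 0.20 | 0.0539 | 11.8% | 2.8% |

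**Power.** Take the difference that the unadjusted formula detects with 80% power: (1.960 + 0.842) × 0.0603 = 0.169 SD. Under stratified randomisation the unadjusted estimate already has the smaller true SD, so its power is Φ(0.842/√(1 − R²)). The adjusted test has power Φ(2.802/√(1 − R²) − 1.960).
- R² = 0.05: Φ(0.863) = 80.6% unadjusted, Φ(0.914) = 82.0% adjusted.
- R² = 0.10: Φ(0.887) = 81.3% unadjusted, Φ(0.993) = 84.0% adjusted.

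The gain is about 1.4 and 2.7 percentage points.

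**Simulation.** Permuted blocks of 4 in six strata were simulated 2000 times per setting (block and stratum sizes assumed). At R² = 0.20 the true SD of the estimate was 0.0533 with or without adjustment. The mean reported SE was 0.0603 unadjusted and 0.0539 adjusted, and type I error was 3.0% and 5.2%. The estimate is as precise either way; only the reported uncertainty is wrong. At R² of 0.02 to 0.10, unadjusted type I error was 5.6%, 4.1% and 4.5%. The Monte Carlo SE is √(0.05 × 0.95/2000) = 0.5 points, so at these smaller values the simulated sizes do not separate clearly from 5%, and the table rests on the formula.

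**Baseline values in Table 2.** Perceived understanding (primary) and objective understanding are measured at ROR1 and ROR2 only, and the actions measures at ROR2 only. Attitudes toward genetic testing, empowerment, decisional conflict, PHQ-8, GAD-2 and PSS-4 are measured at all three visits. Adjustment for the outcome's own baseline is therefore possible for these additional outcomes and impossible for the primary one.

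**Baseline-only measures.** RCT survey measures places the baseline survey before pre-test counselling, and Study arms places GUÍA at result disclosure, about three months later. The four measures precede the intervention and have no later value. The separate support item drawn from the decisional conflict scale is measured at all three visits and is not affected.

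**The case against.** The best defence is that the covariate list is open: it is introduced by *including*, so disease category and site are unnamed rather than excluded. A journal article may also leave the final list to an analysis plan that is not shown. This stands as far as it goes. It rules out saying that the strata will be ignored. It does not remove the mismatch: the article commits to naming covariates, names others, makes them conditional and allows an unadjusted test.

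A reader might infer that baseline scores already collected for the main comparison are being wasted. Table 2 does not support that, since neither the primary outcome nor the secondary outcomes it lists have a baseline score. For the additional outcomes that do, repeated-measures ANOVA is among the stated methods and may already use the baseline values.

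A reader might also infer that standard errors will certainly be too large, or that the result would be invalid. Neither follows. The excess depends on an R² that the article does not give and is zero if the strata are not prognostic. Where it exists, it makes the test conservative and leaves the estimate unbiased.

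Health literacy and numeracy were not stratification factors, so leaving them out does not distort the test's size. Adjusting for them is a choice made for precision.

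On the baseline-only measures, one can say that Table 2 plainly mixes outcomes with descriptors, as its sociodemographic block shows. But these four sit under outcome domains, and the comparison rule excepts only economic impact.

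**Conclusion.** The point holds as a matter of efficiency and consistency, and no validity error has been shown. The strata used for randomisation should appear in the analysis, and the article does not commit to this. If they explain 0 to 10% of outcome variance, leaving them out inflates the reported SE by 0 to 5.4% and lowers true size from 5.0% to between 5.0% and 3.9%, at a cost of up to about 2.7 points of power at the difference examined. These figures assume a continuous outcome, 550 analysed per arm, a two-sided 5% test and no further loss of alpha to multiplicity.

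The baseline-only inconsistency depends on no assumed figure: the comparison rule and Table 2 cannot both be followed meaningfully for those four measures.

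**What to change.** 1. State that every RCT arm comparison adjusts for disease category and clinical site as randomised, and remove the conditional qualifier for these two factors. For categorical outcomes, use a stratified test or a regression model in place of a plain chi-squared test.
2. Add the baseline value of the outcome where Table 2 has one, for example for attitudes, empowerment, decisional conflict, PHQ-8, GAD-2 and PSS-4. For perceived and objective understanding, health literacy and numeracy are optional; if used, they should be fixed in advance. The strata come first, because they are set before the baseline visit.
3. Reconcile the comparison rule with Table 2: relabel decision self-efficacy, patient activation, life chaos and the mMOS-SS as baseline covariates, and take them out of the between-arm comparisons and the multiplicity family.

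The cost is wording in the analysis plan and in the Table 2 labels. Every variable is already collected.
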